The Bhagavad Gita offers practical guidance on navigating daily stressors [12]. Within the realm of RSIs, recent studies offer insights into the potential relevance of the Bhagavad Gita’s teachings for psychological well-being among adolescents [13] and individuals coping with chronic illnesses [14]; however, these studies do not encompass a synthesis of empirical data to validate their findings. Recently, Das and Behura proposed that learning the Bhagavad Gita could improve the stress coping abilities of healthcare providers during the COVID-19 pandemic, drawing parallels between their experiences and those of war veterans; however, this study also lacked empirical substantiation [15].

Considering that homelessness also poses significant challenges to human health, including mental health, and our organization’s volunteers had noted that a significant number of PEH had turned to spirituality as a coping mechanism to deal with the mental health challenges brought about by the COVID-19 pandemic, we hypothesized that imparting the teachings of the Bhagavad Gita as a one-time intervention could enhance the psychological resilience of PEH.

This study aims to bridge the knowledge gap concerning the effectiveness of Hindu RSIs in a previously unexplored population—PEH—by evaluating the impact of learning the Bhagavad Gita on reducing psychological distress among PEH. Engaging in Kuchipudi dance practice as a hobby will function as a positive control, while abstaining from stress-reducing activities will serve as the negative control. In other words, the central research question is, what is the impact of learning the Bhagavad Gita on reducing psychological distress among PEH, and how does this compare with the impact of engaging in Kuchipudi dance practice as a hobby? This multi-site parallel-group RCT seeks to comprehensively assess both short and long-term outcomes. Table 1 outlines the research inquiries guiding our study and presents potential interpretations of the anticipated results.

**Table 1 pone.0310795.t001:** Study design.

Question	Hypothesis	Sampling plan	Analysis plan	Interpretation given to different outcomes

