Does learning the Bhagavad Gita reduce psychological distress in people experiencing homelessness	The immediate post-intervention, delayed post-intervention, and long-term follow-up Kessler psychological distress scale scores will be significantly lower than baseline Kessler psychological distress scale scores	54 participants each in the Bhagavad Gita group, Kuchipudi dance group, Both Bhagavad Gita and Kuchipudi dance group, and Control group for 80% power and 5% alpha	The within-group differences will be analysed by repeated measures analysis of covariance, with continued practice and religion as covariates. Subgroup analyses will be conducted by stratifying the participants in each group by age, religion (Hindu, Non-Hindu), educational attainment, and employment. Post-hoc power analyses will be conducted to verify the robustness and reliability of the subgroup analyses	If we find significant within-group differences in the Kessler psychological distress scale scores, it would suggest that learning the Bhagavad Gita has a potential impact on reducing psychological distress in people experiencing homelessness. Additionally, if our subgroup analyses reveal significant differences based on age, religion, educational attainment, and employment, it would imply that the intervention’s effectiveness varies across these subgroups

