### Interventions

The participants in the Gita group will be imparted the teachings of the second chapter of the Bhagavad Gita (all verses) for 1 week, for 60 minutes per day. The teachings of the Bhagavad Gita will be imparted by a trained teacher and the second chapter has been chosen as it is said to contain the essence of the entire Bhagavad Gita [16]. The participants in the Kuchipudi group will be taught the Kuchipudi dance choreography to a popular devotional song (“Sivashtakam”, choreographed by Padma Bhushan [name] [name], song duration is approximately 10 min) for 60 minutes per day by a trained teacher for 1 week. Every day for 1 week, the participants in the Both group will be taught the Kuchipudi dance choreography to a popular devotional song (“Vandanamu Raghunandana”, choreographed by Kala Tilakam [name], song duration is approximately 5 min), which is shorter in duration than the song used in the Kuchipudi group, for 30 minutes by a trained teacher, followed by imparting the teachings from selected verses of the second chapter of the Bhagavad Gita (Verse 40–72) for 30 minutes by a trained teacher. The participants in the control group will receive no intervention. The participants will be instructed to join their assigned groups at the scheduled meeting times using the meeting link in their sealed envelopes. Apart from the teaching sessions, meetings will also be scheduled one day before the start of the teaching sessions, one day after the end of the teaching sessions, 40 days after the end of the teaching sessions, and 1 year after the end of the teaching sessions for the purpose of recording the baseline, immediate post-intervention, delayed post-intervention, and long-term follow-up measurements, respectively. For participants in the control group, the meeting schedule will consist of only the four measurement sessions.

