### Statistical methods

#### Data analysis

All results will be reported in accordance with the CONSORT guidelines to ensure comprehensive and transparent reporting of the trial’s outcomes. Descriptive summaries of baseline characteristics will be presented to provide an overview of the study population. The comparisons will be between each intervention group and the control group, as well as within each intervention group over time. The repeated measures data will be analysed using the generalised estimating equation (GEE) framework. For the analysis of the primary outcome using the GEE framework, robust standard errors will be used to account for correlated data. Pairwise post-hoc comparisons will be conducted to identify specific group differences. To control for the risk of type I error in these multiple comparisons, the Bonferroni correction will be applied. Subgroup analysis will be conducted using analysis of covariance (ANCOVA) or non-parametric ANCOVA [19] depending on the normality of the data; this may include stratification by age, educational attainment, religion, and employment status. Multiple comparisons will also be addressed using appropriate statistical corrections. These may include the Bonferroni correction, Holm’s adjustment, or the Benjamini-Hochberg procedure, depending on the specific comparisons and the number of tests conducted. The data analysis will be conducted using Python 3.9.13. Statistical significance will be set at a two-tailed p < 0.05.

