### Primary analysis

GEE Framework: The primary outcome, psychological distress as measured by the K10 scale, will be analyzed using the GEE framework. Robust standard errors will be used to account for correlated data due to repeated measures. An exchangeable correlation structure will be assumed.Primary Comparisons: Comparisons will be made between each intervention group (Gita, Kuchipudi, and Both) and the control group. Within each intervention group, comparisons over time (pre-intervention, immediate post-intervention, 40 days post-intervention, and 1-year post-intervention) will be performed.Pairwise Post-Hoc Comparisons: Pairwise post-hoc comparisons will be conducted following significant GEE results to identify specific group differences. The Bonferroni correction will be applied to control for the risk of type I error in these multiple comparisons.

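### Table 1 answers whether the Gita reduces distress by change from baseline within the Gita group, and nothing ties the planned Gita v Control contrast to that question

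*Protocol article*

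**What the plan says.** Table 1 (Introduction), first row, asks a causal question: "Does learning the Bhagavad Gita reduce psychological distress in people experiencing homelessness". The remaining columns answer it from one arm:

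- **Hypothesis:** at all three follow-ups, "Kessler psychological distress scale scores will be significantly lower than baseline Kessler psychological distress scale scores".
- **Analysis:** "The within-group differences will be analysed by repeated measures analysis of covariance, with continued practice and religion as covariates".
- **Interpretation:** "If we find significant within-group differences in the Kessler psychological distress scale scores, it would suggest that learning the Bhagavad Gita", followed by words to the effect of a potential impact on distress.

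In this row the control arm appears only in the sample-size entry. The other rows compare Gita with Kuchipudi, participants who continue practice with those who do not, and Both with each single intervention.

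Elsewhere the article gives the control arm a clear job. The Introduction says that "abstaining from stress-reducing activities will serve as the negative control". The Interventions section has that arm measured at the same four times: "For participants in the control group, the meeting schedule will consist of only the four measurement sessions". Under Data analysis, "The comparisons will be between each intervention group and the control group, as well as within each intervention group over time". Under Primary analysis, the Primary Comparisons item says "Comparisons will be made between each intervention group (Gita, Kuchipudi, and Both) and the control group", and then adds comparisons over time within each intervention group. The Sample size calculation is framed as a 7-point difference between groups.

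**The concern.** Change from baseline in one arm combines any effect of the teaching with everything else that moves K10 over the same period. Two such sources are plausible here. One is a time trend over a follow-up of one year after a disturbed period. The other is the effect of completing the same self-report scale four times. Both act on the control arm as well, so the Gita v Control difference removes them and the within-group change does not.

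If K10 falls equally in both arms, the first row supports an impact of the Gita while the control contrast shows none. The article does not say which result answers the question. The row also names a different model (repeated measures ANCOVA) from the one in the primary analysis (GEE), so it cannot be taken as shorthand for the GEE contrast. The article describes itself as a registered report, and Table 1 is where it fixes how results will be read.

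**Working it through.** **1. Which contrast answers which question**

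| Place | Contrast | Uses Control? |
|---|---|---|
| Table 1, row 1 | Gita follow-up v Gita baseline | No |
| Table 1, row 2 | Gita v Kuchipudi | No |
| Table 1, row 3 | Continued v not continued practice | No |
| Table 1, row 4 | Both v Gita and v Kuchipudi | No |
| Data analysis | Each intervention v Control; within-group over time | Yes; no |
| Primary analysis | Each intervention v Control; within-group over time | Yes; no |

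The right contrast exists in the statistical sections but is attached to no stated hypothesis.

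**2. Inputs for an illustration**

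- From the Sample size calculation: n = 54 per group, correlation 0.5, two-sided alpha 0.05, target difference 7 points.
- Assumed, because the article gives neither: K10 SD of 6, 8 or 10, and a fall common to all arms.
- True Gita v Control effect: zero.

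The article states no error rate for the within-group rule, so there is no figure to reproduce for that. The 54 is taken as the planned number only. The printed formula with its printed inputs gives 7.84 × 22.5 / 12.25 = 14.4, not 53.3. That is a separate matter and does not affect this point.

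**3. One follow-up time**

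SD of change = SD × √(2(1 − 0.5)) = SD, so the standard error is SD/√54 = SD/7.348.

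P(significant fall) = Φ(fall/SE − 1.96). This counts falls only, so its value with no drift is 2.5%.

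For a shared 3-point fall:

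| SD | SE | fall/SE | Probability |
|---|---|---|---|
| 6 | 0.816 | 3.67 | Φ(1.71) = 96% |
| 8 | 1.089 | 2.76 | Φ(0.80) = 79% |
| 10 | 1.361 | 2.20 | Φ(0.24) = 60% |

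A shared 2-point fall gives 69%, 45% and 31%. A 4-point fall gives 99.8%, 96% and 84%. With Bonferroni over three follow-ups, the 3-point fall at SD 8 still gives 64%.

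**4. All three follow-ups significant, as the hypothesis is worded**

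Under a common correlation of 0.5, any two changes from baseline have covariance SD²(0.5 − 0.5 − 0.5 + 1) = 0.5 SD², so they correlate at 0.5. With the same fall at each follow-up, the trivariate normal probability compares with the single-time figure as follows:

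| Shared fall | One time point | All three |
|---|---|---|
| 0.25 SD | 45% | 21% |
| 0.38 SD | 80% | 61% |
| 0.50 SD | 96% | 90% |

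**5. The control contrast under the same drift**

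A simulated Gita v Control test of change (54 per arm, SD 8, shared falls of 0 to 4 points, 10,000 runs each) rejected in 4.7% to 5.1% of runs, two-sided. The shared fall cancels.

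**The case against.** The strongest reply is that the correct comparison is already planned. Both statistical sections list each intervention v Control first, the model is GEE, and the trial is framed around a between-group difference. Gita v Control will be estimated whatever Table 1 says. The row is also worded softly, as suggesting a potential impact. This stands, and it limits the point to a mismatch between Table 1 and the analysis sections, plus the missing ranking of within-group comparisons. It does not remove the mismatch.

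A reader might infer more than the documents support:

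- **That the control arm would remove attention effects.** It would not. Controls attend only the measurement sessions, while the Gita group has daily taught sessions for a week. Only the Kuchipudi arm bears on attention.
- **That regression to the mean is a main threat.** Entry requires no K10 threshold and people with a diagnosed mental illness are excluded, so there is no selection on high scores.
- **That recovery after the pandemic is documented.** The Introduction reports only that distress rose during and after it. An upward drift would make the within-group rule miss an effect rather than invent one.
- **That Gita v Kuchipudi is left to post-hoc testing.** Table 1, row 2, gives it a hypothesis, GEE and ANCOVA, and an interpretation. It is only absent from the Primary Comparisons item.

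It is also fair to object that the calculation is a simple paired test without the covariates in the row. It shows the mechanism and does not predict this trial's error rate.

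**Conclusion.** The point holds in limited form. As written, the first row of Table 1 lets a within-group change answer a causal question, and the statistical sections do not say that the control contrast takes precedence. With no Gita effect, a shared fall of 3 points, under half of the 7-point target, would satisfy that rule at a single follow-up with probability about 60% to 96% for SDs of 10 down to 6. Requiring all three follow-ups lowers the probabilities but leaves them far above nominal. These sizes rest on assumed SDs and drift, the plan's correlation of 0.5 and normal theory. That a shared fall counts as a Gita effect under the row's rule, but not under the control contrast, does not depend on them.

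The documents do not support the stronger conclusion that the trial ignores its control arm or is committed to declaring a benefit from pre-post change.

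**What to change.** 1. **Table 1, row 1:** restate the hypothesis, analysis and interpretation as Gita v Control, estimated as the group-by-time contrast from the GEE in the Primary analysis section.
2. **Primary analysis:** keep all three intervention v Control contrasts as primary, and add Gita v Kuchipudi to match the central question in the Introduction and row 2 of Table 1.
3. **Data analysis and Primary analysis:** make within-group change descriptive (mean change with confidence interval) and give it no efficacy reading.

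Adjusting for baseline K10 is an optional improvement and is not needed to resolve this point.

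The cost is wording in one table row and two sections. No new data or visits are needed. Adding Gita v Kuchipudi raises the number of primary contrasts from three to four, so the Bonferroni count should be stated accordingly.

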Is learning the Bhagavad Gita better at reducing psychological distress than engaging in a hobby in people experiencing homelessness	The decrease from baselines to immediately post-intervention, delayed post-intervention, and long-term follow-up Kessler psychological distress scale scores will be significantly larger in the Bhagavad Gita group than in the Kuchipudi dance group	54 participants each in the Bhagavad Gita group, Kuchipudi dance group, Both Bhagavad Gita and Kuchipudi dance group, and Control group for 80% power and 5% alpha	Intergroup differences will be analysed by the generalised estimating equation and analysis of covariance with continued practice and religion as covariates. Subgroup analyses will be conducted by stratifying the participants in each group by age, religion (Hindu, Non-Hindu), educational attainment, and employment. Post-hoc power analyses will be conducted to verify the robustness and reliability of the subgroup analyses	If our hypothesis holds true, it would suggest that learning the Bhagavad Gita is more effective at reducing psychological distress than engaging in a hobby for people experiencing homelessness. By conducting subgroup analyses, we will further investigate if the effectiveness of the intervention varies based on age, religion, educational attainment, and employment

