Does continued practice influence the effect of the interventions in people experiencing homelessness	The decrease from baselines to delayed post-intervention and long-term follow-up Kessler psychological distress scale scores will be significantly larger in all intervention groups in participants who continue the practices learned during the intervention compared to that in participants who do not continue the practices learned during the intervention	54 participants each in the Bhagavad Gita group, Kuchipudi dance group, Both Bhagavad Gita and Kuchipudi dance group, and Control group for 80% power and 5% alpha	Participants in each group will be subdivided based on whether or not they continued practice during each follow-up. Repeated measures analysis of variance will be conducted on the subgroups	If our hypothesis holds true, it would suggest that sustained practice contributes to greater psychological well-being. Conversely, if there are no significant differences in the decrease of the Kessler psychological distress scale scores between participants who continue and those who do not continue the practices, it would indicate that continued practice does not play a significant role in the effectiveness of the interventions

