### Outcomes and measures

The primary outcome is psychological distress measured by the Kessler scale of psychological distress (K10) in this study. The K10 is a 10-item questionnaire that measures psychological distress based on questions about anxiety and depressive symptoms. It has previously been used in research conducted with PEH [17, 18]. At the immediate post-intervention, delayed post-intervention, and long-term follow-up measurements, apart from the K10, the participants will be asked if they have continued practicing the techniques learned during the intervention (Kuchipudi group: continued practice of the choreography, Gita group: continued self-reflection on the teachings of the Bhagavad Gita, Both group: continued practice of the choreography and continued self-reflection on the teachings of the Bhagavad Gita, and control group: none). The study flowchart is presented in Fig 2.

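### Table 1 rows 2 and 4 adjust comparisons between active arms for continued practice, a post-randomisation mediator defined differently in each arm; row 3 then reads a self-selected split causally

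*Protocol article*

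**What the plan says.** Table 1 (Introduction) sets one analysis per research question.

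- **Row 2** (Gita v Kuchipudi) and **row 4** (Both v each single intervention): "Intergroup differences will be analysed by the generalised estimating equation and analysis of covariance with continued practice and religion as covariates".
- **Row 1** (change within the Gita group): "The within-group differences will be analysed by repeated measures analysis of covariance, with continued practice and religion as covariates".
- **Row 3** (does continuing matter?): it predicts larger K10 decreases in the intervention groups among those who continue. The method is "Participants in each group will be subdivided based on whether or not they continued practice during each follow-up", followed by repeated measures analysis of variance. If the prediction holds, "it would suggest that sustained practice contributes to greater psychological well-being". If there is no significant difference, the row concludes that continuing has no important part in how well the interventions work.

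Outcomes and measures defines the variable. At the three post-intervention measurements, "the participants will be asked if they have continued practicing the techniques learned during the intervention". What counts depends on the arm: "Kuchipudi group: continued practice of the choreography"; self-reflection on the teachings for Gita; both activities for Both; "and control group: none".

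The Data analysis section and the Primary analysis section of the SAP describe a GEE for K10, with each intervention group compared with control. Neither names any covariate, and neither withdraws or qualifies Table 1.

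**The concern.** Whether someone goes on practising is decided after allocation. It depends on what they were taught and plausibly on how distressed they are at the time. If practice lowers distress, as row 3 predicts, it is part of how assignment works, and conditioning on it takes that part out of the estimate. If practice is only a marker of better prognosis, conditioning on it makes arms with different practice rates non-comparable. Randomisation protects against neither.

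The variable also lacks a common meaning across arms. A yes means dancing in one arm, reflecting in another, and both in the third. If the Both arm needs both activities for a yes, its condition is harder to meet, so equal rates cannot be presumed. Nor does the variable have a value at baseline, although baseline is one of the measurement times in the repeated-measures analysis.

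Row 2 is at stake in particular: the Introduction names the comparison of Gita with Kuchipudi as part of the central research question.

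**Working it through.** No stated figure in the protocol depends on this point, so there is none to reproduce. The check has two parts.

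**1. The passages side by side**

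| Place | Comparison | Covariates named |
|---|---|---|
| Table 1, row 1 | within Gita, over time | continued practice, religion |
| Table 1, rows 2 and 4 | active v active | continued practice, religion |
| Data analysis; SAP, Primary analysis | each active arm v control, and within arm | none |

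The randomised contrasts that carry the covariate are those in rows 2 and 4.

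**2. Size, by simulation**

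From the protocol: 64 per arm (recruitment target) and two-sided 5%. Assumed, because the document does not give them: K10 SD 8; one follow-up visit; an unmeasured prognostic factor U explaining 25% of outcome variance; log-odds of practising rising by 0.5 or 1.0 per SD of U; practice of 70% v 30% (or 50% v 50%) at average U. There were 3000 runs per setting.

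Outcome = -(effect x arm) - (practice effect x practice) - 0.5 x 8 x U + error, with error SD 8 x sqrt(0.75). It was regressed on arm, with and without practice. Negative values favour the first arm, which has the higher practice rate in the 70/30 settings.

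| Active v active setting | Without practice | With practice | Rejection, without / with |
|---|---|---|---|
| Null, 70/30, selection 0.5 | 0.0 | +0.7 | 5.4% / 7.9% |
| Null, 70/30, selection 1.0 | 0.0 | +1.1 | 5.7% / 11.3% |
| Null, 50/50, selection 1.0 | 0.0 | 0.0 | 4.7% / 5.0% |
| True -3.5, 70/30, selection 1.0 | -3.5 | -2.4 | 70% / 36% |
| 7 points per practiser, no other effect, 70/30, no selection | -2.8 | 0.0 | 45% / 6% |

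The results follow a simple identity: adjusted minus unadjusted = -(practice coefficient) x (difference in practice rates).

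- Full mediation: the unadjusted effect should be -7 x (0.70 - 0.30) = -2.8, and adjustment removes all of it.
- Null, selection 1.0: the shift is 1.14 - 0.03 = 1.11, and practisers score 3.33 lower. The implied rate difference is 1.11 / 3.33 = 0.33. It is below 0.40 because averaging over U pulls both rates towards 50%.

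In this model, equal rates give no shift. If the link between practice and outcome differs by arm, a single pooled coefficient describes neither arm, and the adjusted contrast no longer has a clear meaning.

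**Row 3.** In the settings where practice has no causal effect, practisers in an active arm still score 1.9 points lower (selection 0.5; significant in 15% of runs) to about 3.4 points lower (selection 1.0; 35 to 38%). A positive row 3 result is therefore expected from selection alone. A non-significant one is weak evidence of no role, because the row has no power calculation of its own: the 54 per group is derived for a 7-point difference between the groups.

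**The case against.** **The primary analysis does not carry the covariate.** This stands. The SAP's primary comparisons are active v control, with no covariates named. A reader might infer that practice, fixed at none in controls, distorts those comparisons. If it were carried there the bias would be larger: under the same assumptions with selection 1.0, a true -7 becomes -5.3 (50% practising) or -4.8 (70%), and a null gives 1.6 points and 15% rejection. But the document does not specify that model.

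**The covariates may attach only to the ANCOVA.** The sentence allows this reading, and the analysis sections use ANCOVA for subgroups. It would spare the GEE, but rows 2 and 4 also give ANCOVA as a method for differences between groups, and that comparison would still be affected.

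**Row 1 uses the same covariates.** It is a within-group analysis, so a reader who infers that a randomised contrast is biased there goes too far.

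**Bias is conditional and its size assumed.** Both are true. It vanishes with equal practice rates and equal links to outcome, and the document gives neither an SD nor a practice rate. Nothing in the design makes three different activities alike in these respects.

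**Row 3 is a separate question in cautious words.** The split can stand as an association. The conclusions attached to both outcomes go beyond it.

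**Conclusion.** The point holds for rows 2 and 4, and separately for row 3. As written, the Gita v Kuchipudi and Both v single contrasts are adjusted for a post-randomisation, arm-specific behaviour that the protocol itself expects to affect K10, so they need not estimate the effect of assignment.

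Under the stated assumptions (SD 8, 64 per arm, 70% v 30% practising) the error is 0.7 to 1.1 points with 8 to 11% rejection under the null. A true -3.5 loses about a third of its size (1.1 / 3.5 = 31%). An effect acting wholly through practice disappears. These sizes are illustrative. The direction depends on which arm practises more.

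It would be too strong to say that every main contrast is wrong: the control comparisons name no such covariate, and row 1 contains no randomised contrast. In row 3, neither the causal reading of a difference nor the reading of non-significance as no role follows from a self-selected split.

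**What to change.** - Delete continued practice from every model that compares randomised groups: rows 2 and 4, GEE and ANCOVA alike. Align Table 1 with the Data analysis and Primary analysis sections so that one between-group model is stated.
- Keep only covariates that the intervention cannot affect, such as religion and site. Baseline K10 also qualifies. It is measured after the allocation envelope is drawn, so it is pre-intervention rather than pre-randomisation. Use it either as a covariate or as a GEE time point, not both, and say which.
- Report continued practice by arm and visit descriptively.
- Relabel row 3 as an exploratory, non-causal association limited to the three intervention arms, since controls have no practice to split on. Remove both of its causal conclusions.

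Cost: wording changes only, with no extra data or participants. Row 3 loses its confirmatory standing.
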